### Primary Outcome measures

Change in the Irritable Bowel Symptom Severity Scale (IBS SSS score) and IBS Quality of Life Questionnaire (IBS-QOL) from baseline to 12 weeks.

The IBS SSS [23] is a 5 item self-administered questionnaire measuring: severity of abdominal pain, duration of abdominal pain, abdominal distension/tightness, bowel habit, quality of life. Maximum score 500: < 75 normal bowel function, 75-174 mild IBS, 175-299 moderate IBS, 300-500 severe IBS). The IBS-QOL[24] is an extensively validated quality of life measure for IBS: 34 items, 8 subscales, item responses graded on a 5 point scale, total score 0-100 with higher scores indicating better health related QOL. Administered at baseline and 6 weeks (end of treatment) and12 weeks (6 months and 12 months would also be planned for the full trial).

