**Methods/Design:**

The aim is to undertake a feasibility factorial RCT to assess the effectiveness of the commonly prescribed medications in UK general practice for IBS: mebeverine (anti-spasmodic) and methylcellulose (bulking-agent) and Regul8, the CBT based self-management website.

135 patients aged 16 to 60 years with IBS symptoms fulfilling Rome III criteria, recruited via GP practices, will be randomised to 1 of 3 levels of the drug condition: mebeverine, methylcellulose or placebo for 6 weeks and to 1 of 3 levels of the website condition, Regul8 with a nurse telephone session and email support, Regul8 with minimal email support, or no website, thus creating 9 groups.

Outcomes: Irritable bowel symptom severity scale and IBS-QOL will be measured at baseline, 6 and 12 weeks as the primary outcomes. An intention to treat analysis will be undertaken by ANCOVA for a factorial trial.

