### Exclusion criteria

Atypical symptoms - (unexplained weight loss, rectal bleeding), diagnosis of inflammatory bowel disease, Coeliac disease or peptic ulcer disease, pregnant or breast feeding, currently taking or allergy to mebeverine or methylcellulose. If patients are already taking mebeverine or methlycellulose but are keen to enter the trial they will be able to do so if they fulfil the inclusion criteria, do not meet any of the other exclusion criteria and they undertake a 4 week mebeverine and methylcellulose free wash out period before entering the trial.

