### Intervention

135 patients will be randomised to: mebeverine (135 mg three times a day), methylcellulose (3 tablets twice a day), or a placebo tablet for 6 weeks. To ensure double blinding, all participants will take three over-encapsulated identical tablets in the morning, one at lunchtime and three at teatime.

They will also be randomised to 1 of 3 website conditions: access to Regul8 with a 30-45 minute nurse telephone session after session 2 (to encourage engagement with the CBT programme) and email support on request, the website with minimal support (i.e. technical email support on request), or no website, thus creating 9 groups.

There will be double-blinding for medication groups, single-blinding for the website (participants will not be able to be blind to website access). Website access will be with a personal password so that usage can be assessed. All patients will receive a telephone call in the first week to check they have no problems with the medication or paperwork. Those not randomised to website access will receive standard patient information and will be offered access to the website at the end of the trial.

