The research nurse will telephone all participants in the trial in the first week after randomisation (see randomisation procedure above) to check they have no problems with the medication or paperwork and to ensure they can log onto the MIBS website. The nurse will also make a time for a phone call session with those randomised to the Regul8 self-management programme with nurse support (see section above for details on telephone session protocol and timing). They will also be able to email the nurse regarding queries about the website programme during the study. Medical questions will not be addressed by the research nurse and participants will be advised to seek medical advice if they have medical queries. Those randomised to website alone will be offered technical website support by email.

Those not randomised to receive the website programme will receive normal GP care. All the randomised participants will receive normal GP care during the trial if they require it.

The trial medication for the MIBS Study is over-encapsulated to maintain blinding but is quite large and preliminary work indicated that some participants may find it difficult to swallow. If participants were considering withdrawal from the trial due to the size of the medication and swallowing problems, they will be permitted to open the medication capsules to enable them to continue to take the medication and stay within the trial. The Research Nurse (RN) will discuss medication taking with any participants who indicate that they are finding it difficult to take. If they indicate that they cannot manage to take the trial medication because of swallowing problems with the capsules, the RN will provide the option that they could open the capsules by twisting them and taking the medication inside the capsule. This is smaller than the entire capsule and thus would mean the medication is easier to swallow and should enable retention of these participants within the study.

These participants will potentially be un-blinded as they will see the tablets. However, participants will be recording their medication taking in diaries and will be asked to guess which medication they are on - enabling assessment as to whether opening the capsule un-blinds the participants. We will record which participants open the capsules. Intention to treat analysis will be maintained but will include the opening of the capsules as factor within the analysis of the data.

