### Analysis

An intention-to-treat analysis, of change in the IBS SSS and IBS-QOL at baseline, 6 weeks and 12 weeks (6 mnth and 1 yr are planned for the full trial) will be undertaken by ANCOVA for a factorial trial. In the main trial (but not in the pilot): subgroup analysis will be performed using regression modelling to determine if symptoms subgroup (diarrhoea-predominate, constipation-predominate and alternating symptoms) predicts differences in outcome. Other potential factors that may affect outcome will be explored: severity of presenting symptoms, duration of presenting symptoms, age and sex.

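### The primary drug-versus-placebo comparison is set at 12 weeks, 6 weeks after treatment ends, and the article's sections disagree on the primary time point

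*Protocol article*

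**What the plan says.** The Intervention section gives the drug arms as "mebeverine (135 mg three times a day), methylcellulose (3 tablets twice a day), or a placebo tablet for 6 weeks". The Trial medication section supplies 6 weeks of capsules, and Primary Outcome measures itself labels week 6 as the end of treatment. Questionnaires fall due 6 and 12 weeks after randomisation (Data collection).

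Three places describe the primary outcome or its analysis:

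- The section on primary outcomes defines a single time point: "Change in the Irritable Bowel Symptom Severity Scale (IBS SSS score) and IBS Quality of Life Questionnaire (IBS-QOL) from baseline to 12 weeks". It sets no separate time point for the drug factor.
- Abstract, Methods/Design: "Irritable bowel symptom severity scale and IBS-QOL will be measured at baseline, 6 and 12 weeks as the primary outcomes".
- Analysis: "An intention-to-treat analysis, of change in the IBS SSS and IBS-QOL at baseline, 6 weeks and 12 weeks", by factorial ANCOVA, with no time point designated as primary.

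For people already using a trial drug, the Exclusion criteria section allows entry if "they undertake a 4 week mebeverine and methylcellulose free wash out period before entering the trial".

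The Sample size section asks for 35 patients per group to detect 53 points with SD 80, for the drug groups and the website groups alike, and states no time point. The following section, on the basis of the assumptions, cites a 68-point advantage of CBT plus mebeverine over mebeverine alone, 6 weeks after the CBT.

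**The concern.** The Aims section sets out to assess each drug against placebo. The effect that a 6-week course can be expected to show most directly is the one present while the drug is being taken. Under Primary Outcome measures, the primary drug contrast instead compares three groups that have all been off trial medication for 6 weeks. That is longer than the drug-free interval the protocol accepts before a prior user may enter.

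Two things are at stake. First, the 80% power stated for the drug contrasts requires a 53-point difference at the moment of measurement. Nothing in the document supports a difference of that size 6 weeks after stopping. Second, because the three sections differ, it is not fixed whether the primary drug result is the week-6 contrast, the week-12 contrast or both.

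The website factor is different. It teaches skills meant to outlast the programme, and week 12 is a reasonable primary time point for it.

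**Working it through.** **Timing.** Planned treatment ends at week 6 and the primary assessment is at week 12: 12 − 6 = 6 weeks off drug. This is 6 − 4 = 2 weeks longer than the washout required of prior users.

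**Inputs (Sample size section).** Difference 53, SD 80, power 80%, 95% confidence (taken as two-sided 5%), dropout 20%, planned total 135. Each factor has three levels, so 135/3 = 45 per level, and 45 × 0.8 = 36 completers per level.

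**Reproducing the plan's figures.** Normal approximation, n per group = 2 × [SD × (1.960 + 0.842)/difference]².

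- IBS SSS: 2 × [80 × 2.802/53]² = 35.8, so 36 (plan: 35).
- IBS-QOL, 10 points with SD 15: 2 × [15 × 2.802/10]² = 35.3, so 36 (plan: 34).
- Total: 3 × 36/0.8 = 135, the planned recruitment.

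The plan's figures are reproduced within two patients per group. The sample size arithmetic is not the problem.

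**Power at week 12 by fraction of effect remaining.** Suppose the on-treatment difference is the planned 53 points and a fraction f of it remains at week 12. The standard error of the difference is 80 × √(2/36) = 18.86. Power = Φ(53f/18.86 − 1.960). The documents give no value for f, so a range is shown.

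| f (assumed) | Difference at week 12 | Difference/SE | Power, normal | Power, t-test | Total N for 80% power |
|---|---|---|---|---|---|
| 1 | 53 | 2.81 | 80% | 79% | 135 |
| 0.75 | 39.75 | 2.11 | 56% | 55% | 240 |
| 0.5 | 26.5 | 1.41 | 29% | 28% | 540 |
| 0.25 | 13.25 | 0.70 | 10% | 11% | 2149 |

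The last column is 3 × n/0.8, with n per level = 36, 64, 144 and 573. IBS-QOL (10 points, SD 15, 36 per level) gives nearly the same power by the normal approximation: 81%, 56%, 29% and 10%. The calculation compares two means and takes no credit for baseline adjustment in the ANCOVA.

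**Source of the 53 points.** The cited 68-point effect is for CBT added to mebeverine, with mebeverine in both arms. It is not a drug-versus-placebo effect, on or off treatment.

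**Timing of the week-6 value.** Under Data collection, an email goes out at 6 weeks, a further reminder follows one week later, and the nurse telephones one week after that. A nominal week-6 value can therefore be collected at 6 + 1 + 1 = 8 weeks, about 2 weeks after the last planned capsule.

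**The case against.** The strongest reply is that nothing is lost. Both scales are collected at week 6 in everyone, and the Analysis section includes that time point in the factorial ANCOVA, so the on-treatment contrast will be estimated. This stands. A reader might infer that the trial misses the drug effect; the documents support only that the effect is not the primary outcome as Primary Outcome measures defines it.

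The washout can also be over-read. It is an entry rule for prior users and does not say that symptom benefit has gone after 4 weeks. It makes a small residual effect plausible without establishing one, so no row of the power table can be called the likely one.

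Week 12 is also a legitimate target if the question is sustained benefit, and the longer follow-up planned for the full trial suggests an interest in durability. On that view the week-12 contrast is not biased; it answers a different question. This stands too, but the article does not say that sustained benefit after stopping is the primary drug question.

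The inconsistency can be softened by reading the Abstract as naming two instruments and their measurement schedule. The wording there, "will be measured at baseline, 6 and 12 weeks as the primary outcomes", does not settle it, and the Analysis section does not resolve it.

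Two further inferences should be resisted. One is that placebo patients will be prescribed the trial drugs in weeks 6 to 12. The text says only "All the randomised participants will receive normal GP care during the trial if they require it", which applies equally during treatment, so this is conjecture. The other is that a null week-12 result would be read as proof that the drugs do not work. No section says so, week-6 results would stand beside it, and the Discussion says the trial is not powered for a definitive effect size.

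**Conclusion.** The point holds in limited form. As defined under Primary Outcome measures, the primary drug-versus-placebo contrast is off treatment by 6 weeks, and the Abstract, Primary Outcome measures and Analysis sections do not agree on the primary time point. The 53-point assumption is tied to no time point and is supported by a CBT effect.

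The loss of power depends on how much drug effect persists, which the documents do not give. It is nil if all persists, and power falls to about 55%, 28% and 10% at three-quarters, half and a quarter. These figures assume a 53-point on-treatment effect, 36 completers per level and no gain from baseline adjustment.

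This should be fixed but is not critical. The Discussion makes feasibility the main output, and the week-6 data already exist in the plan. It still matters because the same section claims power for moderate to large effects and expects the pilot to yield effect estimates for a larger trial.

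**What to change.** - Name one primary time point per factor: week 6 (end of treatment) for mebeverine and methylcellulose versus placebo, and week 12 for the website conditions. Make the other time point secondary for each factor.
- Use the same statement in the Abstract, Primary Outcome measures and Analysis sections.
- In the Sample size section, say which time point the 53 points refers to for each factor.
- Record the completion date of each week-6 questionnaire, so that values obtained after treatment has ended can be identified.

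The cost is wording and one date field. No assessment, treatment or recruitment target changes, and 135 patients keep about 80% power if the drug difference at week 6 is 53 points. The downside is that sustained drug benefit becomes a secondary question. If sustained benefit is what the sponsor wants as primary, the protocol should say so and justify a 53-point difference 6 weeks after treatment ends.

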### Secondary outcome measures

The Subjects Global Assessment of Relief (SGA of Relief)[25] is frequently used in treatment trials to identify IBS responders to therapy. Participants rate their relief from IBS symptoms on a scale of 1 to 5 ranging from "completely relieved" to "worse". Scores are dichotomized so that patients scoring from 1-3 are considered responders and those 4-5, non-responders.

The Hospital Anxiety and Depression Scale (HADS)[26] is a commonly used self-report instrument for detecting depression and anxiety in patients with medical illnesses. It enables assessment of participants' level of anxiety and depression which has shown to be high in many patients with IBS.

Patient Enablement Questionnaire[27] assesses participants' ability to cope with their illness and life. The number of Primary Care consultations for IBS will also be assessed to look for any change. Other studies have shown an impact on GP contacts from patient self management programmes [22].

The acceptability of the Regul8 self-management treatment will be assessed using three questions where patients rate the overall effectiveness of the programme, the efficacy of programme compared to other treatments they have tried, and whether they enjoyed the programme.

Qualitative interviews will also be undertaken at the end of treatment with a small number of the participants regarding their experience of participating in the trial and the acceptability of the trial procedures, including the medication taking. This will provide richer and more detailed information on the trial experience and provide valuable information to inform a full trial.

Up to 30 participants will be invited to participate, using purposive sampling to ensure we sample people with a range of age, gender, symptoms and treatment combinations. The interviews will be semi-structured with open ended questions covering the following topics: Main reasons to try out the treatment; Expectations of the treatment before initially trying it; Positive and negative perceptions of the treatment; Changes during and after the end of treatment; Looking back at the treatment (thoughts and feelings). The set of generic questions will be repeated for each treatment type that is mentioned by the participants and for the intervention received during the trial.

All interviews will be tape-recorded and full transcribed, and inductive (data driven) thematic analysis will be used to analyse the data following the methods described by Boyatzis (1998)[28], Braun and Clarke (2006)[29], and Joffe and Yardley (2004)[30].

### Sample size

The aim of the pilot is to have sufficient numbers to test the feasibility of the trial and assess crude differences between the groups. Assuming an initial mean symptom score of 250 (SD 80) in all groups, 35 patients are required in each group to detect a difference in score of 53 points (2/3 of a SD of 80) between the treatment groups (mebeverine, methylcellulose and placebo) or the three website groups (none, minimal support, telephone) for 80% power and 95% confidence. Allowing for drop outs at 20%, 130 participants would be needed. If 135 are recruited each of the 9 randomisation groups would potentially have 15 recruits.

For IBS-QOL, 34 would be required in each group to detect a 10 point change in the IBS-QOL in the intervention group assuming a score in the placebo group of 60 (SD of 15). Hence, allowing for a 20% drop-out rate, again 135 participants would be more than sufficient.

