### Basis of assumptions for power calculation

The Kennedy[12] paper (2005) using the symptom score in general practices in London found a baseline symptom score of approximately 300 (SD 80) in the IBS SSS in their trial of cognitive behavioural therapy and mebeverine and a treatment effect of a 68 point reduction for CBT and mebeverine together over mebeverine alone at 6 weeks after the CBT. (Their a priori power calculation was on the basis of a score of 180 (SD80) in the control group and 133 (SD80) in the CBT (treatment) group at 6 months follow up.)

The IBS-QOL overall score was found to be 63.2 (SD 18.5) in validation scores for the measure[24], and a pre-treatment score of 65.8 (SD19.9) with a post-treatment score 10.2 points higher was found in further validation of the measure in female patients with functional bowel disorder in secondary care assessing cognitive behavioural or patient education versus desipramine or placebo[31].

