## Discussion

IBS is a common problem managed largely in general practice. Many patients live with significant restrictions on their daily activities and reduced quality of life. There is a lack of research evidence on the commonly prescribed medications and a lack of availability of psychological therapies such as CBT which have been shown to be beneficial in IBS. Provision of a web-based CBT self-management programme for IBS patients has the potential to open up new resources for IBS patients with minimal additional cost in an area where there is significant ill-health burden. Clarifying the effectiveness of commonly prescribed medications will allow better informed prescribing decisions and targeting of NHS resources.

This pilot study is the first to look at providing CBT as a web-based self-management programme for patients with IBS. The factorial design allows the effectiveness of common IBS medications to be assessed at the same time, maximising the amount of data collected. The trial will answer important questions regarding the feasibility of undertaking this type of research, which requires the involvement of large numbers of patients from many GP practices across different PCTs. Trial systems will be tested and data will be collected about recruitment and drop-out rates, reasons for declining to take part, acceptability of the medication and of the outcome measures. Data on the variance and estimated effects of the intervention will also be able to be assessed. It will also provide guidance on the amount of support/therapist time that is likely to be required for the self-management programme. The qualitative data will highlight useful changes in the self-management programme or the study design for a larger trial. This is a pilot study and the feasibility issues will be the main useful outcomes as the trial is not powered to detect a definitive effects size. It will however, have power to demonstrate whether there are moderate to large effects.

The trial methods comply with best practice for the conduct and reporting of RCTs and thus will provide good quality data and will be able to be replicated on a larger scale.

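### The IBS-QOL sample size rests on an SD of 15 that the protocol's own stated basis (18.5 and 19.9) does not support, so the claim that 135 patients are ample does not follow

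*Protocol article*

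**What the plan says.** The protocol article's section on primary outcome measures names two: IBS SSS and IBS-QOL, each as change from baseline to 12 weeks.

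The Sample size section first sizes the trial on IBS SSS, "for 80% power and 95% confidence". It then turns to IBS-QOL and says that "34 would be required in each group to detect a 10 point change in the IBS-QOL in the intervention group". The same sentence goes on to give the inputs behind that number, "assuming a score in the placebo group of 60 (SD of 15"). It concludes that, "allowing for a 20% drop-out rate, again 135 participants would be more than sufficient".

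The section headed Basis of assumptions for power calculation gives two sources for IBS-QOL. The first: "The IBS-QOL overall score was found to be 63.2 (SD 18.5) in validation scores for the measure". The second: "a pre-treatment score of 65.8 (SD19.9) with a post-treatment score 10.2 points higher was found in further validation", in women with functional bowel disorder in secondary care.

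The Analysis section plans an ANCOVA for a factorial trial. It gives no correlation between baseline and follow-up.

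**The concern.** The SD is the input that drives the calculation, and the value used is smaller than both values offered in its support. For IBS SSS the SD of 80 in the calculation is the SD of 80 in the cited trial. For IBS-QOL no such link exists: 15 appears once, without a source or an explanation. It is described as the SD of the score in the placebo group, not as a residual SD after baseline adjustment.

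The effect has a similar gap. The calculation needs a difference between groups, and the basis section supplies none for IBS-QOL. Its one figure close to 10 is a rise from before to after treatment. Such a rise includes whatever improvement untreated patients would also show.

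At stake is how the IBS-QOL result is read when the full trial is planned. If readers believe the pilot had 80% power for 10 points, they may give a null result more weight than it deserves. If SD 15 were carried into the full trial and the true SD were 18.5 to 19.9, the required number would be too small by a factor of (18.5/15)² = 1.52 to (19.9/15)² = 1.76.

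**Working it through.** **Inputs from the protocol article**
- Target difference 10 points, SD 15, 34 per group (Sample size).
- 80% power and 95% confidence, stated for IBS SSS and taken to apply to IBS-QOL; two-sided 5% is assumed.
- 135 patients, 20% drop-out, three equal levels per factor: 135/3 = 45 randomised per level, and 45 × 0.8 = 36 completers per level.
- Cited SDs 18.5 and 19.9 (Basis of assumptions for power calculation).

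**Step 1: the plan's own figure.** The normal-approximation formula is n = 2(1.960 + 0.842)² (SD/difference)². With SD 15 and 10 points, n = 2 × 7.849 × 2.25 = 35.3, so 36 per group. The t-test gives 36.3, so 37. The stated 34 is close. A one-sided test would give 28 and 90% power would give 48, so the plan's figure corresponds to an unadjusted two-sided comparison of two groups at 80% power. At 36 completers per level, t-test power is 79.7%. On its own input the plan roughly holds.

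**Step 2: the same calculation with the cited SDs.** Two-sample t-test, two-sided 5%, 10 points:

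| SD | Difference in SD units | Power, 36 per level | Power, 45 per level (no drop-out) | n per level for 80% | Total with 20% drop-out |
|---|---|---|---|---|---|
| 15 | 0.667 | 79.7% | 87.9% | 37 | 139 |
| 18.5 | 0.541 | 61.9% | 71.8% | 55 | 207 |
| 19.9 | 0.503 | 55.7% | 65.5% | 64 | 240 |

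The totals are 3n/0.8, rounded up.

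**Step 3: detectable difference.** With 36 per level, 80% power corresponds to 0.6696 SD. That is 0.6696 × 18.5 = 12.4 points, or 0.6696 × 19.9 = 13.3 points.

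**Step 4: what ANCOVA could recover.** With correlation r between baseline and follow-up, the residual SD is SD × √(1 − r²). It equals 15 when r = √(1 − (15/SD)²):
- SD 18.5: r = √(1 − 0.657) = 0.59
- SD 19.9: r = √(1 − 0.568) = 0.66

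The document gives no r, so the values below are assumptions. Power for 10 points with 36 per level, t-test on the residual SD:

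| Assumed r | SD 18.5: residual SD, power | SD 19.9: residual SD, power |
|---|---|---|
| 0 | 18.5, 62% | 19.9, 56% |
| 0.5 | 16.0, 74% | 17.2, 68% |
| 0.6 | 14.8, 81% | 15.9, 75% |
| 0.7 | 13.2, 89% | 14.2, 84% |

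**The case against.** **ANCOVA is the planned analysis.** This is the strongest objection, and it stands in part. A reader might infer from Step 2 that the trial has 56 to 62% power and not 80%. The documents do not support so flat a statement: those figures belong to the unadjusted comparison, and under ANCOVA power could exceed 80%. But it cannot be assumed either, because no correlation is given and 15 is presented as the SD of a score.

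**The arithmetic is not wrong.** Correct. With SD 15 the result is 36 to 37 against a stated 34. The fault is an unsupported input, not a miscalculation.

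**The sources may not describe this trial's patients.** Also fair. The 19.9 comes from women in secondary care, while this trial recruits both sexes from general practice. The plan also departs from its sources elsewhere, taking an IBS SSS mean of 250 where its source had about 300. So the mismatch does not prove 15 wrong. It shows that 15 has no stated reason, and both available figures point the other way.

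**The 10 points may be a chosen target.** It may. A reader might infer that it was taken from the 10.2-point rise, but the text does not say so, nor which patients the 10.2 describes. What remains is that no between-group IBS-QOL difference is offered in support.

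**It is a pilot.** The Sample size section limits the aim to feasibility and crude differences, and the Discussion says the trial is not powered for a definitive effect. That lowers the consequence. It does not reconcile the sufficiency claim with the figures beside it.

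**The Discussion's power sentence.** A reader might extend the point to "It will however, have power to demonstrate whether there are moderate to large effects". That would be wrong. The detectable effect of about 0.67 SD with 36 per level does not depend on the SD, and it fits that description.

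**Conclusion.** The point holds as an unsupported planning assumption for a primary outcome. The two IBS-QOL SDs offered as the basis are both larger than the one used, and no reason is given. On those SDs, "again 135 participants would be more than sufficient" does not follow: unadjusted power for 10 points is about 56 to 62%, and 80% power needs a true difference of about 12.4 to 13.3 points.

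This rests on two-sided 5% testing, 20% drop-out spread evenly over the factor levels, pairwise comparison of two levels, and the cited SDs applying to this population. True power under the planned ANCOVA cannot be fixed from the document. It reaches 80% if the correlation is about 0.59 (SD 18.5) to 0.66 (SD 19.9) or more.

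Given the pilot aim, the matter is worth correcting but does not threaten the trial.

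**What to change.** Keep 135 patients, the design and the analysis. In the Sample size and Basis of assumptions sections:

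1. Either justify SD 15, for example as a residual SD after baseline adjustment with the assumed correlation and its source, or restate the IBS-QOL figure. The restatement would be: with SD 18.5 to 19.9 and 36 completers per level, unadjusted power is about 56 to 62% for 10 points, and 80% for about 12 to 13 points. Add the ANCOVA range with its assumption, for instance about 74% and 68% at r = 0.5.
2. Remove the claim that 135 is more than enough for IBS-QOL.
3. State that 10.2 is a within-group change and that 10 points is a chosen target difference.

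The Discussion sentence on moderate to large effects can stay as it is.

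The cost is text only. The downside is that the stated IBS-QOL power becomes less favourable.
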